### Determination of sample size

This is a hypothesis-generating registry from which preliminary data will be obtained that will be key to refining values used for estimating statistical power for future multicenter clinical trials. It is anticipated that these data may be useful in identifying medical, endovascular, and health system interventions that could be tested in a future randomized clinical trial, providing more accurate estimates of expected detectable differences and their standard deviations. Therefore, a formal power analysis was not undertaken in the design of this pilot registry.

### Statistical analysis

Descriptive statistics will be presented as means and standard deviations for continuous variables, and frequencies and percentages for categorical data. Continuous data that are not normally distributed will be analyzed by nonparametric methods. Key time variables will be analyzed as continuous variables, and also categorized to allow assessment of dose–response patterns. Univariate models for all outcome variables with demographic, clinical and risk factor variables will be used to elucidate potential confounding variables. Multivariable logistic regression models will be used to assess the association between key time variables and short-term binary outcomes (amputation, MI, stroke and death), with adjustment for confounders. Survival analysis will be performed using Kaplan-Meier methods for preliminary analyses, and Cox proportional hazards models with adjustment for confounders. Multiple linear regression models will be used to assess the associations between time segment variables and length of stay, with adjustment for confounders. A two-sided p-value of <0.05 will be considered statistically significant. Data analysis will be performed using Stata (Stata Inc, College Station, TX, USA).

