Ambulatory status on admission and discharge will be obtained from patient self-report and supplemented by abstracted medical record reports of treating clinicians. There is at present no single well-accepted format for recording ambulatory status in individuals with ALI and CLI. Ambulatory status therefore will be categorized into five groups and assigned ordinal values of 1 to 5, with 5 representing the best, and 1 the lowest, ambulatory status. The highest class (5), “fully ambulatory”, is defined as the ability to independently ambulate and fully interact in the community. “Minimal ambulation” (4) is defined as ambulation limited to within the house/hospital, around the house/hospital, and to the mail box. “Ambulation with assistance” (3) is defined by ambulation requiring another person’s help for mobility. “Wheelchair bound” (2) is defined by dependency on a wheelchair for all mobility. “Bed bound” (1) is defined when the patient is not mobile at all, is fully restricted, and non-ambulatory. Ambulatory status at baseline is the level of function after onset of ALI or CLI and within one week prior to admission. Data will be abstracted by trained research staff and reviewed by vascular physicians.

All data will be collected via a standardized case report form and then entered into a password-protected database. Data will be collected consistent with the intersocietal “2012 ACCF/AHA/ACR/SCAI/SIR/STS/SVM/SVN Key Data Elements and Definition for Peripheral Atherosclerotic Vascular Disease” standards [14]. Outcome events will be reviewed and adjudicated by a clinical event committee consisting of individuals with expertise in vascular surgery and vascular medicine. The registry design has been approved by the local institutional review board at the University of Minnesota and Allina Health System. All included patients will provide written informed consent. Patients screened for entry who do not offer informed consent will be entered into a screening log.

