### Key time segments

The symptom onset of an initial episode of ALI/CLI is defined by the patient’s self-report provided to the vascular specialist at hospital admission, is dictated into the encounter note, and this note (date and time) is later abstracted from the medical records. Vascular specialists (vascular surgeons, vascular medicine specialists, and interventional radiologists) are instructed to document the patient-reported index limb symptom onset within pre-specified time parameters: within one hour for patients presenting within 3 days, within one day for patients presenting within 3 to 30 days, and within one week for patients presenting greater than one month since symptom onset. For CLI patients who cannot state an exact time of leg symptom onset, it will be assumed that the onset time is 12 noon on the day specified. Inasmuch as ALI or CLI is known to recur (repeat episodes are common), the index leg symptom is arbitrarily defined as that which is temporally closest to the index hospitalization. This approach is similar to that used for ACS or stroke health services research.

While the pre-admission symptom duration serves as the primary pre-defined hypothesized predictor of advanced PAD health outcomes, a number of other clinical care time segments are considered of potential utility in evaluation of the efficiency of hospital-based PAD care, as it is known that CLI hospitalizations are lengthy (greater than seven days) and expensive [15]. The “admission to ABI/TBI” time segment is defined as the time from hospital arrival to initiation of the first hospital-based pedal or toe pressure measurement. The “admission to heparin” time is defined as the time from hospital arrival to the chart-documented initiation of a therapeutic intravenous heparin infusion for patients so treated. The “admission to vascular specialist at bedside” time segment is defined as the time from hospital arrival until the patient is evaluated by a vascular specialist, and this is set by the time of the dictated note. The “admission to revascularization” time segment is defined as the time from hospital arrival until the patient enters the operating room or catheterization laboratory, and includes only the use of an endovascular procedure, surgical procedure or primary amputation (medical treatment alone is not included in this definition). Hospital length of stay is defined as the number of days of hospitalization from admission to discharge.

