**Demographic, clinical and functional characteristics, and key time segments**						
Demographic variables						
	Race, gender, education	X				
	Marital and employment status	X	X	X	X	X
Physical examination (weight, height, blood pressure, heart rate and rhythm)		X				
Laboratory values (serum creatinine, hemoglobin, fasting lipid profile)		X				
Etiology of ALI-CLI		X				
Key time segments (see ‘List of key time segments’)		X	X			
Length of hospital stay			X			
Endovascular and open surgical procedures			X			
Ambulatory status		X	X	X	X	X

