We hypothesize that the current arbitrary 14 day diagnostic “time-based syndrome definition” that is often used to differentiate ALI and CLI (beyond use of the 6 “Ps”) may not adequately discriminate these two syndromes. The rationale for use of the 14-day timeframe to define ALI has not been based on evidence as robust as the data used to define the efficacy of acute MI or stroke treatments. While there was a biological rationale for setting an objective 14-day, time-based inclusion criteria for study of catheter-directed thrombolysis in individuals with acute arterial occlusion [20,25], this time-based definition has been carried forward into subsequent PAD care guidelines without corroborating the utility of this approach for endovascular and open surgical techniques.

This registry provides an opportunity to assess whether ALI or CLI are indeed two distinct clinical syndromes with different etiologies and outcomes, or whether these traditional clinical distinctions alternatively represent a time-dependent continuum of advanced PAD.

More than 20 years ago, Panetta et al. [26] observed that a longer duration of ischemia was associated with increased amputation rates in ALI patients, and a more recent study suggested that an increased duration of limb ischemia was associated with more extensive gangrene [27]. Nevertheless, these observations were derived from small cohorts, did not clarify a precise vulnerable period, nor elucidate other factors that might affect limb outcomes. This registry may provide insights into factors that, along with prolonged pre-admission limb ischemia, worsen prospects for limb survival. The registry will also provide a contemporary description of current etiologies of limb ischemia. For example, does atrial fibrillation contribute to limb ischemic events at a rate documented a decade ago, now that antithrombotic therapies are more widely used? Is graft surveillance used, per current national care guidelines, at rates adequate to protect individuals who have undergone prior successful limb revascularization?

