During the last decade, cardiovascular care guidelines have become an important cornerstone of the management of heart disease and the positive impact of guidelines is known [28]. In contrast, the development and dissemination of PAD care guidelines, including recommendations regarding the ideal management of ALI and CLI, are rarely evaluated prospectively [1,2]. These guidelines have recognized that appropriate use of evidence-based risk-reduction medication represents a major opportunity for reducing future myocardial infarction, stroke, and death if used in individuals with recognized PAD. However, recent data have shown poor rates of use of evidence-based risk-reduction medication on admission or discharge in patients with CLI [10,29,30]. The registry will provide an opportunity to evaluate the contemporary use of risk-reduction medications to prevent these major ischemic events in the PAD population at highest short-term risk. We hypothesize that higher use of these medications would offer a potentially major contribution to improvement in rates of amputation-free survival; only a prospective registry with an adequate cohort sample is likely to provide such data, as a prospective RCT to evaluate this hypothesis is currently unlikely. Data further demonstrating such benefits of risk-reduction medication use might then be considered for future guideline inclusion, or within future PAD performance standards [31].

Currently there are no standardized quality-of-life instruments that are widely applied in populations of individuals with critical limb ischemia. This registry offers an opportunity to evaluate functional status on admission, at discharge and at follow-up, as well as other predictors of functional status at follow-up. While it is known that poor ambulatory status on presentation is associated with loss of primary patency and higher rates of amputation at six months follow-up, other factors beyond patency (e.g., avoidance of readmission, social support, etc.) may contribute to the achievement of improved functional outcomes [32].

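### The univariate outcome screen for confounders does not exclude variables measured after symptom onset, so adjusting for them may remove part of the symptom-duration effect

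*Protocol article*

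**What the plan says.** The Statistical analysis section gives one step for finding confounders: "Univariate models for all outcome variables with demographic, clinical and risk factor variables will be used to elucidate potential confounding variables". It then applies the result: "Multivariable logistic regression models will be used to assess the association between key time variables and short-term binary outcomes", with adjustment for confounders. The Cox models and the linear models for length of stay are adjusted in the same way. No timing restriction is placed on the candidate variables.

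The main exposure is set under Key time segments: "While the pre-admission symptom duration serves as the primary pre-defined hypothesized predictor of advanced PAD health outcomes". Two kinds of variable recorded at admission bear on it:

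- **Ambulatory status.** Under Use of source documents and data abstraction: "Ambulatory status at baseline is the level of function after onset of ALI or CLI and within one week prior to admission". The Discussion adds that "poor ambulatory status on presentation is associated with loss of primary patency and higher rates of amputation at six months follow-up".
- **Tissue loss.** Table 1 lists ulcer and gangrene among the clinical symptoms and signs for all patients. The Discussion cites a study suggesting that "an increased duration of limb ischemia was associated with more extensive gangrene".

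**The concern.** A confounder must be related to the exposure, must affect or stand in for a cause of the outcome, and must not be a consequence of the exposure. The stated step examines only the relation to the outcome. It can therefore bring in variables that the exposure itself has changed, and it can miss confounders that show only in a joint model.

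This matters most for symptom duration. A longer wait with an ischemic limb may produce gangrene and loss of walking, and these in turn may lead to amputation. They are then part of how delay does harm. A model that holds them fixed estimates only the remaining, direct part of the effect. The registry is meant to supply estimates for later trials and to identify delay as a possible target, so an unrecognized shift in this estimate would carry forward.

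**Working it through.** **No figure to reproduce.** The protocol gives no effect size, sample size or power figure on this point. The check sets the definitions side by side and then asks what adjustment could do under assumed values.

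**Step 1: timing.** Exposure is the interval from symptom onset to admission. Ambulatory status is taken after onset and within a week before admission, so it falls inside or at the end of that interval. Ulcer and gangrene are recorded at enrollment, at the end of it. None of these is fixed before the exposure begins.

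**Step 2: would the screen reach them?** Ulcer and gangrene are labelled clinical, a class that the rule names. Ambulatory status is less clear. Table 2 puts it in a block headed "Demographic, clinical and functional characteristics, and key time segments", and the rule does not name functional variables. It is neither named as a candidate nor excluded.

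**Step 3: would ambulatory status be selected if screened?** Assume a p<0.05 cut-off (the protocol sets none for this step), an amputation risk of roughly 20%, and five classes with shares 10, 15, 20, 25 and 30%. The simulated chance of selection (400 replicates each) is:

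| Log odds ratio per class | n=100 | n=200 | n=400 |
|---|---|---|---|
| −0.3 | 39% | 64% | 93% |
| −0.5 | 74% | 96% | 100% |

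**Step 4: effect of adjusting.** All inputs are assumptions. X is standardized duration. M is ambulatory class 1 to 5, cut from a latent function score with slope a on X. Amputation risk is 20%, and log-odds(Y) = i + 0.2·X + b·(M − 3.5). In the frailty settings a standard normal pre-onset variable U also enters: X = (noise + 0.5·U)/√1.25, latent function falls by 0.5 per unit of U, and 0.3·U is added to the log-odds. There are 200,000 patients per setting. Share removed = (ln OR_total − ln OR_with M)/ln OR_total. With frailty, the total OR is the one adjusted for U.

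| a | b | No frailty: total OR | with M | share removed | Frailty: OR without M or U | total OR | with M | share removed |
|---|---|---|---|---|---|---|---|---|
| 0 | −0.3 | 1.22 | 1.23 | −4% | 1.49 | 1.23 | 1.37 | −55% |
| 0 | −0.5 | 1.21 | 1.23 | −10% | 1.52 | 1.20 | 1.36 | −71% |
| −0.2 | −0.3 | 1.31 | 1.22 | 26% | 1.59 | 1.31 | 1.35 | −13% |
| −0.2 | −0.5 | 1.36 | 1.22 | 35% | 1.70 | 1.36 | 1.35 | 2% |
| −0.4 | −0.3 | 1.39 | 1.21 | 42% | 1.67 | 1.39 | 1.32 | 15% |
| −0.4 | −0.5 | 1.52 | 1.22 | 53% | 1.84 | 1.48 | 1.31 | 32% |
| −0.6 | −0.3 | 1.48 | 1.22 | 49% | 1.74 | 1.44 | 1.30 | 29% |
| −0.6 | −0.5 | 1.68 | 1.22 | 62% | 2.00 | 1.63 | 1.30 | 46% |

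The ends of the no-frailty range with a below zero are (ln 1.31 − ln 1.22)/ln 1.31 = (0.270 − 0.199)/0.270 = 26% and (ln 1.68 − ln 1.22)/ln 1.68 = (0.519 − 0.199)/0.519 = 62%. Shares were computed before the odds ratios were rounded. A negative share means that the adjusted estimate lies above the total effect.

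**Step 5: reading the table.** Without frailty, adjustment returns roughly the direct effect, e^0.2 = 1.22, and the mediated part is lost. With a = 0 nothing is lost. With frailty, M is partly a stand-in for U, and the error runs in either direction. In three of the eight frailty settings the total effect lies below both estimates, so reporting the two does not guarantee that they enclose it.

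**The case against.** **The step may be only exploratory.** It is said to point to potential confounders. No threshold is given, and nothing says that a univariate association alone puts a variable in the model. Final covariate lists are commonly left to an analysis plan that is not shown. This stands in part: the absence of a list is no finding. The stated step is still the only one described, and it searches on the wrong criterion. The threshold that does appear, "A two-sided p-value of <0.05 will be considered statistically significant", is for results and is not stated to govern selection.

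**Ambulatory status may never be screened.** This also stands. It is labelled functional, and functional status is itself an outcome in the secondary aims. The point does not depend on it alone, because ulcer and gangrene are named as clinical signs.

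**Adjustment may help.** Function after onset also reflects function before onset, and frail patients may both delay and do badly. This stands and is the strongest objection. In seven of the eight frailty settings the estimate with M was closer to the total effect, on the log scale, than the estimate with no covariates at all. A model adjusted for pre-onset covariates would recover some of that, by an unknown amount.

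**It is a pilot.** The protocol calls the registry hypothesis-generating under Determination of sample size. That lowers the stakes. But the abstract also calls it hypothesis-driven with pre-specified factors, and its estimates are intended for use in later trials.

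**Conclusion.** The point holds as a risk that the stated method leaves open. Searching for confounders by univariate association with outcomes neither tests association with the exposure nor keeps out variables that may be consequences of symptom duration. The protocol itself supplies the timing and the outcome association for ambulatory status, and a link from longer ischemia to gangrene.

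A reader might infer that the plan will adjust for ambulatory status and so bias the duration effect toward zero by a known amount. The documents do not support that. They do not name ambulatory status as a covariate, they give no figure relating duration to function, and under plausible frailty the adjusted estimate can lie above the total effect. The 26% to 62% range rests wholly on assumed inputs with no frailty, and the loss is nil if duration does not affect function. This is worth correcting before the analysis; it does not undermine the registry.

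**What to change.** Replace the univariate screen with an adjustment set chosen in advance, on subject-matter grounds, for each hypothesis.

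- **Symptom duration, primary models.** Use recorded variables that precede symptom onset, for example age, sex, diabetes, history of coronary or cerebrovascular disease, PAD before the index episode, smoking history and etiology. Table 2 takes creatinine at admission, so it does not qualify as pre-onset. Leave out post-onset ambulatory status and tissue loss.
- **Sensitivity analysis.** Repeat the duration models with post-onset ambulatory status and tissue loss added, and report both sets together. State that the first aims at the total effect and that a difference may reflect mediation, confounding or both.
- **Pooled model.** Do not rely only on models within ALI and within CLI. The protocol separates these syndromes at 14 days' duration, so splitting on them conditions on the exposure. Report a pooled model as well.

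The cost is a change of wording and a little more analysis. Some residual confounding by pre-onset function will remain, and the sensitivity model deals with it only in part. A new question on walking before onset would help only future patients: recruitment began in February 2007, and those already enrolled would lack it.

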#### List of pre-specified “key time segments” for patients with advanced peripheral artery disease

Symptom onset to admission

Admission to ABI/TBI measurement

Admission to IV heparin administration

Admission to vascular specialist at bedside

Admission to revascularization

Length of stay (days)

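### Length of stay is regressed on in-hospital intervals that are part of the same stay, so a test of the slope against zero cannot show that delay prolongs the later course

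*Protocol article*

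**What the plan says.** The Statistical analysis section of the protocol article commits to this model: "Multiple linear regression models will be used to assess the associations between time segment variables and length of stay, with adjustment for confounders". It sets two-sided p<0.05 as the criterion for significance. It does not limit the predictors to the pre-admission segment.

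The Key time segments section defines the outcome: "Hospital length of stay is defined as the number of days of hospitalization from admission to discharge". The same section defines four intervals that start at the same moment and end during the hospital course:

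- pressure measurement: "time from hospital arrival to initiation of the first hospital-based pedal or toe pressure measurement"
- heparin: "the time from hospital arrival to the chart-documented initiation of a therapeutic intravenous heparin infusion for patients so treated"
- vascular specialist: "time from hospital arrival until the patient is evaluated by a vascular specialist"
- revascularization: "time segment is defined as the time from hospital arrival until the patient enters the operating room or catheterization laboratory"

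The list of pre-specified segments that follows contains these four, one interval that ends before the stay begins ("Symptom onset to admission"), and length of stay itself. The Key time segments section gives the purpose of the in-hospital intervals as judging how efficient hospital care is, and notes that CLI stays exceed seven days and are costly.

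**The concern.** An interval that starts at arrival and ends inside the stay is a component of the stay. A regression of the whole on one of its parts gives a positive slope even when the part has no bearing on what happens afterwards. This is not confounding. For any fixed set of covariates the segment is still contained in the outcome, so adjustment leaves the built-in slope in place. A larger sample only makes it more significant.

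What is at stake is interpretation. The Determination of sample size section hopes that the data will help identify health system interventions for a later randomized trial. A significant coefficient for time to revascularization could be read as evidence that delay worsens recovery, although the test against zero does not address that question.

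**Working it through.** The article gives no sample size, expected coefficient or segment duration for this model, so there is no stated figure to reproduce. The check is algebra plus a simulation under assumed inputs.

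**Algebra.** Let S be the time from arrival to the event and R the stay after it, so stay = S + R. Then

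slope of stay on S = Cov(S + R, S) / Var(S) = 1 + slope of R on S.

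If delay has no effect on the later course, the slope of R on S is 0 and the slope of total stay is 1. A test of the total-stay slope against 0 is therefore a test of whether each day of delay shortens the remaining stay by exactly one day. That is not the question of interest.

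**Inputs.** From the article: two-sided 0.05, and CLI stays above seven days. Assumed: mean stay 8 days; S and R independent and lognormal; CV of R 0.8; CV of S 1.0 (0.5 as sensitivity); mean S of 0.25, 1, 2 or 3 days; n = 100, 200 or 400; stay rounded to whole days; 2,000 runs per setting.

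**Approximation.** With S and R independent, z ≈ SD(S) × √n / SD(R). At n = 200 (√n = 14.14) and CV of S 1.0:

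- mean S 0.25: SD(R) = 0.8 × 7.75 = 6.2; z = 0.25 × 14.14 / 6.2 = 0.6
- mean S 1: SD(R) = 0.8 × 7 = 5.6; z = 1 × 14.14 / 5.6 = 2.5
- mean S 2: SD(R) = 0.8 × 6 = 4.8; z = 2 × 14.14 / 4.8 = 5.9
- mean S 3: SD(R) = 0.8 × 5 = 4.0; z = 3 × 14.14 / 4.0 = 10.6

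**Simulation, no true effect of delay, CV of S 1.0.** Share of runs with p<0.05 for total stay on S, slope tested against 0:

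| Mean segment (days) | n = 100 | n = 200 | n = 400 | Mean R² at n = 200 |
|---|---|---|---|---|
| 0.25 | 8% | 9% | 13% | 0.01 |
| 1 | 40% | 68% | 93% | 0.04 |
| 2 | 94% | 99.9% | 100% | 0.15 |
| 3 | 99.9% | 100% | 100% | 0.36 |

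The mean slope was 0.99 to 1.06 in every setting. With CV of S 0.5 and n = 200, the shares were 26%, 82% and 99.8% for mean segments of 1, 2 and 3 days.

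**Controls.** With R as the outcome, the mean slope was -0.007 to 0.06 and p<0.05 occurred in 4.1% to 5.4% of runs. Testing the total-stay slope against 1 gave 4.4% to 5.4%. A pre-admission segment independent of stay gave 4.3% at n = 200. The excess thus comes from the overlap and not from skewness or rounding.

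**Several segments in one model.** With three nested segments entered together (n = 200; means about 0.25, 1 and 2 days), the longest carried the built-in slope: 0.99, with p<0.05 in 81% of runs. The two shorter ones averaged 0.08 and -0.01, with p<0.05 in 6% and 5%.

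**The case against.** The strongest defence is that total stay is a legitimate quantity for the stated purpose. If a day's wait adds a day in a bed, earlier treatment does save bed-days, and the slope describes that correctly. The slope is also not fixed at 1. It can fall below or above 1 according to what delay does to the remaining stay, so the estimate carries information. The article speaks only of associations and claims no effect on recovery. All of this stands, and it limits the criticism to the test against zero and to what is read from it.

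It also stands that the affected model is minor. Length of stay is not among the aims in the Background or the outcomes named in the text of the Study outcomes section. Pre-admission symptom duration, the primary hypothesized predictor, lies outside the stay. The registry is described as a hypothesis-generating pilot.

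Three stronger readings are tempting and are not supported:

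- A reader might infer that significance is a foregone conclusion for every in-hospital segment. The article gives no durations, spreads or sample size. For a mean segment of a quarter-day the test rejects in only 8% to 13% of runs, and in a joint model the shorter segments stay near 5%.
- A reader might infer that length of stay is planned as a predictor of short-term death, because it is on the segment list and key time variables enter the logistic models. Taken that literally, the plan would also regress stay on itself, and Table 2 keeps key time segments and length of stay on separate rows. This is loose labelling, not a planned circular model.
- A reader might count the absence of a log-scale or gamma model, or of competing-event handling for in-hospital death, as part of the error. Those are choices a condensed article may leave to the analysis plan.

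**Conclusion.** The concern holds in limited form. From the article's own definitions, the planned regression has an expected slope of 1 for in-hospital segments when delay has no further effect, so p<0.05 against zero cannot show that delay prolongs the later stay. That part is algebra and needs no assumed figures.

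How often a misleading significant result would follow does depend on assumptions. It is frequent when the segment varies on the scale of days, which is plausible mainly for admission to revascularization, and rare when it varies by hours. The slope remains valid as a description of total bed-days. Neither the analysis of symptom onset to admission nor the amputation-free survival analyses are touched. Severity: should fix, in a secondary exploratory analysis.

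**What to change.** In the Statistical analysis section:

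- For in-hospital segments, above all admission to revascularization, use the stay after the event as the outcome, for example from entry to the operating room or catheterization laboratory until discharge. Alternatively, keep total stay and test the slope against 1.
- Keep total stay as the outcome for symptom onset to admission.
- State that length of stay is an outcome in this model and not one of its predictors.
- If the total-stay slope is also reported, describe it as bed-days and not as evidence about recovery.

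The cost is a change of wording and slightly more analysis work. The remaining stay is length of stay minus the segment, and both are already defined as registry variables. The article defines stay in days and does not mention a discharge clock time, so for segments of a few hours the remaining stay will hardly differ from the total. Those are also the segments where the problem is small.
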